
(especially mental health disorders), and ~10% of VHA patients are enrolled in Medicaid, our results will be of interest to the Centers for Medicare and Medicaid Services.

**2.4. Overview of Study Design and Timeline.** We propose a 3-year mixed methods study (timeline shown in Figure 2) of the Choosing Wisely Initiative and its implementation, which constitutes a natural experiment. We have chosen a Type III Hybrid design in order to focus the assessment of the initiative on implementation while at the same time providing information about the effectiveness of different elements of the initiative's toolkit. We recognize that this initiative is being undertaken without prior studies of the toolkit's efficacy. However, we also recognize that toolkits have been a prominent part of VA's quality improvement efforts along with quality

[figure not shown]

The Choosing Wisely Initiative, which will roll out April 1, 2014, will allow facilities to choose one of two overuse/low value care issues to address: reducing risk of adverse drug effects related to diabetes overtreatment and reducing MRI use in low back pain evaluation. Thus, for Aim 1, we will compare outcomes across four different groups of facilities: those who choose (1) overtreatment for diabetes; (2) MRI overuse for low back pain; (3) both; or (4) neither. Randomization is impractical, and implementation will vary among facilities both in terms of what is implemented and when it is implemented. Because intervention exposure will not be random, we will use special care in design, reporting and interpretation of evidence in accordance with MRC Guidance and draw causal inferences cautiously. As such, this observational study will assess effectiveness rather than establish causality. For the purposes of the study, we consider the first year of the initiative to be the implementation phase. This will be followed by a 12 month sustainability phase.

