For Aim 1 we will use a hierarchical ordinal logistic regression approach using patient-level longitudinal data (4/1/14 to 3/31/2015) to model the probability of overtreatment (and undertreatment) in which Choosing Wisely Initiative participation status (focus on overtreatment of diabetes, overuse of MRI for low back pain, both, or neither) is the key predictor variable of interest. Using patient-level data will provide power to identify even modest differences between groups. Aim 2 will utilize similar methods to assess associations with the facility characteristics of commitment to quality, teaching intensity, and safety culture. Aim 3 will utilize facility-level (cross-sectional) aggregate data (4/1/13 to 3/31/2016). High and low performers will be identified based on changes in overtreatment rates pre- and post-initiative (rather than on absolute values). In order to minimize issues related to regression to the mean as well as floor and ceiling effects, we will focus on facilities that were mid-performing at baseline (2nd and 3rd quartiles). We will focus on those facilities which had high reductions in overtreatment rates at 12 months (high performers) and those who had low (or negative) reductions in overtreatment rates, i.e., got worse, (low performers). Surveys and phone interviews will be conducted to assess what practices were (or were not) implemented to reduce overtreatment, as well as what barriers and facilitators existed to following the initiative. (DM-QUERI has committed funds to support pre-funding work, including instrument refinement and testing - see support letter). Field testing will continue in year 1. The purpose of the surveys of high and low performing sites is to provide the data for the qualitative comparative analysis (QCA) to assess which factors contribute to the difference in performance. Data from semi-structured interviews and site visits will enhance the interpretation. At year 2, the findings of the QCA will be assessed in depth via site visits to the high performing sites, with artifact collection, procedural observation, and in person semi-structured interviews conducted with clinicians (including CPSs, PCPs, and clinic managers), to enhance understanding of contextual factors. Our overall approach is based on the methods developed and used by the

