**2.4.1. Innovation and Toolkit.** The innovation is the de-intensification of glycemic control to prevent hypoglycemia in vulnerable patients. The toolkit provides materials and recommendations to facilitate implementation. Our conceptual model, which is based on a diffusion/dissemination of innovation model, incorporates a focus on the provider, who along with his/her patient makes decisions about de-intensification of therapy. This focus is based on the Theory of Healthcare Professionals' Behavior and Intention, a modification of the Theory of Planned Behavior (Figure 1). Ever since the Diabetes Control and Complications Trial in 1993, the close relationship between glycemic control and DM complications (consequences to patients) has been stressed in the academic literature (knowledge source) with continuing medical education support from professional societies, advocacy groups, and by pharmaceutical manufacturers (knowledge sources of varying credibility and social influence). Practice guidelines (knowledge source) reflect the interests of these and other stakeholders. General recommendations of target A1c levels have been made by specialty societies and governmental agencies both in the United States and elsewhere. It is in this context that Choosing Wisely is being conducted and for which the toolkit is being developed. The toolkit is evolving and includes a variety of materials and more general recommendations, some of which were developed from the bottom up and others from the top down, reflecting the need for multifaceted approaches and allowance for local adaptation. (See Toolkit materials in Appendix.) Although the individual elements have support in the literature, we note that they have not been tested as a package, hence our choice of a Hybrid III study design. Nevertheless, this is the toolkit that will be used in the initiative, and our conceptual model will inform the facility- and provider-level assessments, as the domains are included in the surveys and interviews of high and low performers. We also expect that important disseminators will include many of the ~1,500 Clinical Pharmacists/ Clinical Pharmacy Specialist (CP/CPS) in 131 medical centers authorized to prescribe in Primary Care and/or Diabetes clinics (PBM – personal communication).

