#### **2.4.9. Qualitative Analyses**

**Aim 3.** To identify configurations of the implementation strategy (Choosing Wisely toolkit), provider characteristics, and organizational level factors that are associated with successful reduction of overtreatment rates by comparing high and low performers. Data collection and analysis for these research questions will use a mixed methods approach, as described below.

***Provider/Clinician/Clinical Manager Surveys.*** Provider surveys (see Appendix) will be administered approximately 1 year following implementation of the initiative to clinical leaders and PCPs and other clinicians at the low and high-performing sites. Survey domains are derived from our conceptual framework. The surveys will obtain data on provider and organizational factors potentially affecting overtreatment rates. Provider characteristics include clinician type (MD, DO, NP, PA, CPS), years in practice, and gender. The survey is based on the Diabetes Attitudes Survey and the Veterans Assessment and Improvement Laboratory (VAIL) VISN 22 Survey of Primary Care Team Experiences. We will also assess clinicians' knowledge and attitudes towards glycemic targets. We will assess efficacy using the Provider Abilities subscale from the Midwest Clinicians' Network Barriers to Diabetes Care Survey questionnaire, adding items modeled after Glazier et al. and questions about factors such as competing priorities. We will use the Consolidated Framework for Implementation Research (CFIR) framework to define potentially influential organizational factors. The survey will consist of questions assessing the potential importance of each CFIR construct in implementing the Choosing Wisely Initiative. This survey has been used in the evaluation of four initiatives (E-Consults, SCAN-ECHO, Specialty Care Neighborhood, and Mini-Residencies) so far in the Specialty Care Evaluation project. We will survey up to 30 individuals in each of the ~30 identified low and high performing sites (~900 surveys). We will conduct the survey online (Inquisit® software) with follow up emails, letters, and phone calls as needed. Respondent burden will not exceed 25 minutes. Respondents will be given the opportunity to enter into a lottery for an iPad or Android Tablet.

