***Semi-Structured Interviews.*** A semi-structured interview guide will be developed consisting of questions designed to obtain input on the organizational and provider factors identified as most important from the surveys. As part of the Specialty Care Evaluation project, we have developed multiple interview guides addressing most of the CFIR constructs. These questions have been used successfully thus far for four different Specialty Care initiatives; for a draft, we have selected potentially relevant questions from these previously developed guides and tailored them for this study (see Appendix). The interviews will also contain questions about which elements of the toolkit have been implemented. Potential respondents (the clinical pharmacy specialist, director of primary care, and primary care providers) will be contacted via an email invitation followed by a phone call. All interviews will be conducted by two research team members, with one conducting the interview (audio-taped) and one taking field notes. Based on our experience with the Evaluation Center and others, we will conduct approximately 5 interviews per facility for the highest and lowest performers (n=150). If saturation is not achieved, we will conduct additional interviews.

***Site Visits.*** Once the analyses have been completed and the key constructs identified (see analysis plan below), we will conduct site visits to the highest performing sites; we will select facilities of various levels of complexity and location. (We have budgeted for 8 visits.) The primary purpose of the site visits will be to obtain detailed information on site-level manifestation of the constructs associated with implementation success. Interviews will be conducted with the clinical pharmacy specialists, primary care providers, and clinical managers. Clinics will be visited and artifacts collected, e.g., education materials, screen shots of CPRS (using test patients) illustrating decision support, clinical reminders, and lab comments on A1c. Site visits will require 2 days by a 2-person team. We will use methods adapted from prior work conducted by colleagues with the Center for Organization, Leadership, and Management Research (COLMR).

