To analyze the *interview* data, our focus will be on coding the data according to components of the Choosing Wisely toolkit and constructs from the CFIR. Most of the interview guide questions will define specific toolkit components and CFIR constructs that will allow the researchers to efficiently collect and evaluate the appropriate data. Following each interview, two members of our research team will review interview notes. Each member of the team independently assigns the appropriate CFIR code(s) to each response. The team then seeks consensus on the codes for all responses for a given interview. Each team member then independently reviews the responses associated with each construct and assigns a 0 or 1 rating to the construct, which reflects the respondent’s perception of the manifestation of the construct in the organization (0 = negative, 1 = positive). Choosing Wisely toolkit components will be assigned either a zero (absent) or 1 (present). Once this process is completed for all respondents at a given site, the team meets to assign an overall rating for each construct at the site level, considering the ratings across respondents and each respondent’s role in and knowledge of the Choosing Wisely Initiative. The findings will be entered into a matrix, with sites as columns, constructs/ components as rows, and ratings (0 or 1) as the cell entries. Data will be analyzed initially using a matrix analysis approach to examine potential correlations of the ratings with performance (i.e., ratings of 1 with high performance and ratings of 0 with low performance).

The matrix will also be analyzed using qualitative comparative analysis (QCA), which is a case-oriented,

[figure not shown]

comparative analytic method based on set-theoretic relationships (as opposed to statistical or correlational relationships) between explanatory factors and an outcome. This approach allows for systematic cross-case comparisons across a small to intermediate number of cases, which is the situation for this study. It is useful for studying causal complexity—when different combinations of factors can lead to the same outcome, when some

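### Toolkit components are coded present or absent, with no adoption date, from interviews held after the 12-month outcome has closed, so late adoption can change a necessity or sufficiency label

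*Protocol*

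**What the plan says.** The order of steps has to be put together from several Protocol sections.

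- **Outcome.** Section 2.4 defines the sites to be studied by their change in overtreatment: "We will focus on those facilities which had high reductions in overtreatment rates at 12 months (high performers", set against sites with little or no reduction.
- **Surveys.** Section 2.4.9 sends these only to the selected sites; they "will be administered approximately 1 year following implementation of the initiative".
- **Interviews.** These come after the surveys, because the guide consists of "questions designed to obtain input on the organizational and provider factors identified as most important from the surveys". On the toolkit, "The interviews will also contain questions about which elements of the toolkit have been implemented".
- **Coding.** Section 2.4.10: "Choosing Wisely toolkit components will be assigned either a zero (absent) or 1 (present". Neither a date nor a reference period is attached.
- **Use.** The ratings are compared with performance in a matrix, used to choose six to eight variables, and entered in the QCA. There a factor is necessary if it is positive at every high performer, and sufficient if high performance follows every time it is present. The analysis is repeated for low performance.

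The Protocol expects timing to differ. Section 2.4 says "implementation will vary among facilities both in terms of what is implemented and when it is implemented", and Section 2.4.1 says "The toolkit is evolving and includes a variety of materials and more general recommendations".

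**The concern.** Research question 3.1 asks which toolkit configurations go with a greater reduction in overtreatment. A component can explain a site's 12-month change only if it was in use early enough to affect it. The coding rule does not separate a component in use from the start of the initiative from one introduced in the last weeks of the year, or between the end of the year and the interview. All three can be coded 1.

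The error can go either way. At a low performer, late adoption records the component as present where performance was poor, which can remove a sufficiency label that the component deserved. In the separate analysis of low performance, it can place the component among the conditions for failure. At high performers, late adoption can fill the last gaps, so that a component used at only some of them during the outcome period looks necessary. The same ratings also decide which variables enter the QCA.

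The labels have consequences. Section 2.4.10 gives as an example that a necessary component might be recommended to all facilities.

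**Working it through.** The plan states no figure on this point, so there is none to reproduce. The check has two parts: whether anything else in the Protocol restores the time order, and how sensitive the strict rules are to late adoption.

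**1. Does any other provision date the components?**

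- Section 2.4.5.2: sites are contacted 3-4 months after the start, but only to establish participation status. Details of local actions are expressly not collected, so there is no contemporaneous record of components.
- Section 2.5: a paired pre-post analysis uses each facility's implementation date. That is one date per facility, not per component.
- Section 2.5: if components are added to the toolkit, or a national measure is adopted, the instruments are to be modified and the analysis time points may be. This covers changes to the toolkit or the wider context, not the date on which a site took up a component.
- Section 2.4: surveys and interviews are to establish which practices were or were not implemented. No period is given.

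None of these ties the 0/1 code to the outcome period.

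**2. How sensitive are the labels?**

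Input from the Protocol: about 5-10 sites per group, roughly 30 in total (Section 2.4.6). The adoption rates below are assumptions, since the Protocol gives none. Sites are taken as independent.

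*Sufficiency of a single component.* Suppose the component was absent from all n low sites during the outcome period, and each low site adopts it late, before the interview, with probability q. The chance that at least one low site is coded 1 is 1 − (1 − q)^n.

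| q | n = 5 | n = 10 |
|---|---|---|
| 0.05 | 1 − 0.95^5 = 0.226 | 1 − 0.95^10 = 0.401 |
| 0.10 | 1 − 0.90^5 = 0.410 | 1 − 0.90^10 = 0.651 |
| 0.20 | 1 − 0.80^5 = 0.672 | 1 − 0.80^10 = 0.893 |

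*Necessity.* Let p be the probability that a high site used the component in the outcome period, and q the probability that a high site without it adopts it before the interview. The component is coded 1 at all n high sites with probability [p + (1 − p)q]^n. With dated coding the probability is p^n. Taking p = 0.8:

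| | n = 5 | n = 10 |
|---|---|---|
| Dated coding | 0.8^5 = 0.328 | 0.8^10 = 0.107 |
| Undated, q = 0.25 | 0.85^5 = 0.444 | 0.85^10 = 0.197 |
| Undated, q = 0.50 | 0.90^5 = 0.590 | 0.90^10 = 0.349 |

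With groups this small and rules that tolerate no exception, one late adopter among the low sites is enough to change a sufficiency label.

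**The case against.** The strongest reply is that the coding rule is silent on timing and does not say that a component counts whenever it was adopted. Section 2.4 gives the purpose of the instruments as explaining the difference in performance, which points interviewers toward practices that could have produced it. The draft interview guide is in an appendix that is not shown, and development of the qualitative codes is a separate scheduled task, so adoption dates could be collected there. The surveys fall close to the end of the outcome year, and how much later the interviews fall cannot be read from the schedule. Aim 3 tests no hypotheses, Section 2.4 commits to caution on causal claims, and Section 2.4.10 returns to interview memos and site visits before specific recommendations are made.

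Much of this stands, and it limits the claim. A reader might infer that late components will be counted as causes, or that low performers will add components in reaction to poor rates and be scored as failures. The Protocol supports neither as a prediction. It gives no rate of late adoption and does not say that results are fed back to sites before the interviews. Nor do recommendations follow straight from the labels.

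The reply does not remove the point. Even if the guide asks for dates, the stated rule does not use them. A shared understanding of purpose is not a coding rule when two raters must assign 0 or 1. Adoption late in the outcome year is affected as well, however soon the interviews follow.

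**Conclusion.** The point holds as a weakness in a rule that the Protocol fixes: exposure is recorded after the outcome, undated, and judged by criteria that allow no exceptions. Late adoption can therefore change a label. How often it would do so is unknown.

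The illustration of about 23-40%, 41-65% or 67-89% rests on assumed late adoption of 5%, 10% or 20%, on 5-10 low sites acting independently, and on a single component absent from all of them in the outcome period. Choice of focus at VISN level would weaken independence. A combination of components is broken only if every part of it is coded 1 at a low site, so combinations are less exposed.

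A reader might take half of the roughly 30 sites as low performers and obtain higher figures. Section 2.4.6 does not give that split and says that the group sizes cannot be known in advance.

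The change is worth making because it is cheap and bears on the main product of Aim 3. It does not undermine Aims 1 and 2.

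**What to change.** 1. At interview, ask for the month in which each toolkit component came into use at the site.
2. In the primary QCA and the matrix that feeds it, code a component 1 only if it was in use for a pre-specified minimum part of the 12-month outcome period. Count from the actual rollout or facility implementation date. A fixed calendar cut-off would be unsafe, because Section 2.5 allows for a delay of up to six months and such a date could score most components 0.
3. Record later adoption in a separate category, and use it only in describing sustainability at year 2.
4. Repeat the QCA with undated coding as a sensitivity analysis, and report any label that changes.
5. Word the items on the organizational (CFIR) constructs to refer to the same outcome period.

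The cost is one question per component in instruments still being refined, plus a short coding rule. The drawback is recall error in the dates. Artifacts can check them only at the visited sites, which are high performers, so dates from low performers would go unchecked.

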**Comorbidities.** Using ICD 9CM codes we will create indicators of advanced complications of diabetes, limited life expectancy, cardiovascular or ischemic vascular disease, and major medical and mental health conditions that would impact benefit or risk of tight control based upon previously published taxonomies.

**Demographic Variables.** We have developed algorithms to process multiple entries of patient data over time and from a variety of sources to optimize the demographic information available for research. Sources include many years of VA inpatient and outpatient data with multiple fields and Medicare data. Consequently, we have nearly complete and largely confirmed assignments for most variables, including age and sex. Because of limitations in data concerning race/ethnicity, we will not assess this variable.

**2.4.6. Identification of High and Low Performers.** High and low performers will be identified based on changes in facility overtreatment rates pre- and post-initiative (rather than on absolute values). Those with the greatest (high performers) and least reduction (low performers) in overtreatment rates will be selected. To

minimize issues related to regression to the mean, we will focus on facilities that were mid-performing at baseline (2nd and 3rd quartiles). See Fig. 4. Among the middle-performing facilities at baseline, we will select those facilities with the greatest reduction in overtreatment rates (high performers) and those with the least reduction (low performers). We will also select from among the highest performers at baseline who improved at all as well as some low performers at baseline who stayed low. It is impossible to know how many facilities will fall into these categories; but we are anticipating approximately 5-10 in each group (total n~30). Aim 3 does not include hypothesis testing, but is instead looking for identifying patterns of provider and facility characteristics associated with performance status (high vs. low). Our methods of analyses (matrix and qualitative comparative analysis) allow for a small sample size. Performance status will be determined independently of Choosing Wisely participation status; selected sites will likely include those facilities choosing the hypoglycemia initiative alone or both hypoglycemia and low back pain initiatives. If entire VISNs participate

[figure not shown]

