factors may only be causal in the presence of other factors, and when the absence of the outcome has a different causal pathway than simply the absence of factors associated with the outcome (i.e., causal asymmetry). We will define approximately six to eight independent variables for use in the QCA. Selection of these variables will be based on the findings from the matrix analysis and will include those toolkit components and those CFIR constructs

that (1) distinguish between low and high performers (i.e., negative or absent in low sites, positive or present in high sites); (2) were absent or negative in most sites, regardless of performance; and (3) were positive or present in most sites, regardless of performance.

QCA will allow us to determine those constructs whose positive manifestations (rating of 1) are *necessary* for achieving high performance. A construct is considered necessary if it is always positive in high-performing sites. That is, high performance cannot occur in the absence of a positive manifestation of the construct, but its presence does not guarantee high performance. QCA will also determine those constructs or combination of constructs that are *sufficient* for achieving high performance. A construct or combination of constructs is sufficient for high performance if high performance always occurs when the positive manifestation of the construct or combination of positive constructs is present. The presence of a sufficient construct or combination of constructs guarantees high performance when the necessary constructs are present. For example, we may find that a particular toolkit component is necessary, but not sufficient for high performance. Thus, a policy recommendation might be to recommend that all facilities at a minimum implement the necessary component, as without it facilities have no chance of success. We may also find that no components are necessary, but three of the available components are sufficient. Thus, a policy recommendation might be to recommend at least one of the three components, and allow facilities to select from among any of the three sufficient components. For example, among the components likely to be necessary, if not sufficient, are clinical reminders and local audit and feedback.

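### The QCA rule in 2.4.10 can readily label combinations sufficient when no construct matters, so its deterministic wording is unsupported and a chance check is needed

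*Protocol*

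**What the plan says.** The relevant text is in the Protocol, sections 2.4.6 and 2.4.10.

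- **Sites.** For the high- and low-performer groups, "we are anticipating approximately 5-10 in each group (total n~30"). The split between high and low sites is not fixed.
- **Coding.** Each team member "assigns a 0 or 1 rating to the construct", and a site-level 0/1 rating is then agreed. Toolkit components are coded absent or present.
- **Number of conditions.** "We will define approximately six to eight independent variables for use in the QCA".
- **Selection.** "Selection of these variables will be based on the findings from the matrix analysis", which relates ratings to performance in the same sites. Criterion 1 takes constructs that "distinguish between low and high performers (i.e., negative or absent in low sites, positive or present in high sites"). Criteria 2 and 3 take those that "were absent or negative in most sites, regardless of performance; and (3) were positive or present in most sites, regardless of performance".
- **Sufficiency.** A construct or combination "is sufficient for high performance if high performance always occurs when the positive manifestation" is present. No number of supporting sites is attached.
- **Reading of the result.** The section says a sufficient combination guarantees high performance once the necessary constructs are present. In an example, it says facilities without a necessary component have no chance of success. Low performance is to be analysed in the same way.

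The Protocol excludes formal hypothesis testing for Aim 3 and quotes no error rate for the QCA.

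**The concern.** Three features work together. There are many possible combinations for few sites. A combination needs only to be free of low sites, however few high sites show it. Part of the condition set is picked because it already separates the outcome in the data to which the rule is then applied.

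A clean-looking solution could therefore appear whether or not any toolkit component or organisational factor matters. The results are meant to inform feedback to operational partners, and the text describes them in deterministic, causal terms. A chance configuration could be passed on as a recipe.

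**Working it through.** **No figure to reproduce.** The Protocol gives no false-finding rate for the QCA, so the check starts from its stated inputs: about 30 sites, 6 to 8 binary conditions, full consistency and no minimum count.

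**Step 1: configurations against sites (no assumptions needed).**
- 6 conditions: 2^6 = 64 rows; at least 64 − 30 = 34 empty, 34/64 = 53%.
- 8 conditions: 2^8 = 256 rows; at least 256 − 30 = 226 empty, 226/256 = 88%.
- Combinations of positive conditions: 2^6 − 1 = 63 and 2^8 − 1 = 255.

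**Step 2: a hand calculation.** Assume 15 high and 15 low sites, and independent ratings unrelated to performance that are positive with probability p. A given set of four positive conditions occurs in a site with probability q = p^4. It counts as sufficient by chance with probability (1 − q)^15 × [1 − (1 − q)^15].
- p = 0.5: q = 0.0625, (1 − q)^15 = 0.380, product 0.236. There are 15 four-condition sets among 6 conditions and 70 among 8, so the expected number of chance-sufficient sets is 15 × 0.236 = 3.5 and 70 × 0.236 = 16.5.
- p = 0.7: q = 0.240, (1 − q)^15 = 0.0163, product 0.0160. The expected numbers are 0.24 and 1.1.

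These are expected counts of overlapping sets, not probabilities. They show that chance findings are easy to obtain and that their number depends strongly on p.

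**Step 3: simulation under noise.** The result is the chance of at least one positive combination found in at least m high sites and no low site. Assumed, because the Protocol does not give them: p, the high:low split, the candidate pool, and the correlation of ratings within a site.

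*Three-way selection:* 2 to 4 separating conditions, the rest 20% or 80% positive; independent ratings.

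| Split | m | 6 conditions | 8 conditions |
|---|---|---|---|
| 15:15 | 1 | 0.76–0.92 | 0.94–0.99 |
| 15:15 | 2 | 0.53–0.87 | 0.78–0.96 |
| 10:20 | 1 | 0.61–0.85 | 0.84–0.95 |
| 10:20 | 2 | 0.27–0.68 | 0.49–0.82 |

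*Every condition chosen as the best separator of 12 candidates, 15:15* (a harsher rule than the Protocol's):

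| Assumption | m | 6 conditions | 8 conditions |
|---|---|---|---|
| p = 0.5, independent | 1 | 0.89 | 0.97 |
| p = 0.5, independent | 3 | 0.76 | 0.90 |
| p = 0.7, independent | 1 | 0.34 | 0.57 |
| p = 0.5, latent correlation 0.3 | 2 | about 0.4 | about 0.5 |
| p = 0.5, latent correlation 0.5 | 2 | 0.16 | 0.23 |
| p = 0.7, latent correlation 0.3 | 2 | 0.05 | 0.08 |

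With no selection at all (p = 0.5, independent, 15:15, m = 1) the rate is already 0.75–0.78 for 6 conditions and 0.93–0.94 for 8. Selection adds to the problem but does not create it.

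**Step 4: necessity.** A construct positive in 80% of sites regardless of performance, as criterion 3 allows, is positive in all of 15 high sites with probability 0.8^15 = 0.035, and in all of 10 with probability 0.8^10 = 0.107. With two such constructs, at least one is called necessary by chance with probability 1 − (1 − 0.035)^2 = 0.07 or 1 − (1 − 0.107)^2 = 0.20. This is less frequent than chance sufficiency, but not negligible for a claim that success is impossible without the construct.

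**The case against.** A reader might infer that the QCA will find sufficient combinations in noise about nine times in ten. The Protocol does not support that figure. It needs independent ratings that are about half positive, an even split, and usually selection of the best separators only. One team rates all of a site's constructs from the same interviews, so correlated ratings are plausible, and the rate then falls sharply. Rarer positive ratings would raise it.

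It is also tempting to say that the conditions are chosen for separating the sites. Only criterion 1 does that; criteria 2 and 3 ignore performance. Nor does it follow that most filled rows hold a single site, since mostly absent or mostly present conditions concentrate sites in fewer rows. The pool of 12 is itself an assumption: section 2.4.10 expects 10 to 12 organisational factors from the surveys, and the matrix also holds an unstated number of toolkit components.

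Aim 3 is openly exploratory, so no error rate is breached. Its policy statements are framed as possibilities, and interviews and site visits add context. A minimum case count could be set in an analysis plan that is not shown.

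All of this stands against a fixed rate or a charge of failed inference. It does not remove the point. The Protocol itself fixes the number of conditions, the same-site selection, the sufficiency rule and the deterministic reading. Returning to memos from sites where a construct was positive, and visiting only the highest performers, cannot expose a chance configuration. A minimum count alone is not enough either: requiring three high sites still leaves 0.76 and 0.90 in the half-positive, independent case.

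**Conclusion.** The concern holds as a conditional one. As written, the rule can readily declare combinations sufficient when no construct matters, and the document does not fix how often.

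Under the three-way selection with independent ratings, the rate is roughly 0.5 to 0.99 for one or two supporting sites. The exception is a 10:20 split with two supporting sites, where it ranges from 0.27 to 0.82. With the best of 12 conditions at 15:15, it is about 0.3 to 0.6 when ratings are 70% positive, and about 0.4 to 0.5 with half-positive, moderately correlated ratings. Stronger correlation, or both features together, takes it lower.

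Even the middle of this span is too high for the claim that a combination guarantees high performance, or that success is impossible without a component. The weakness limits how Aim 3 can be interpreted. It does not affect Aims 1 and 2.

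**What to change.** Amend section 2.4.10 as follows.

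1. **Label-shuffling check.** Shuffle the high/low labels across sites (for example 1,000 times). Each time, repeat the matrix screening, the choice of conditions and the QCA. Report descriptively how often shuffled data give a solution with at least the observed coverage. Shuffling keeps the actual share of positive ratings and their correlation within sites, so none of the assumptions above is needed.
2. **Supporting sites.** Report the number of high sites behind each configuration, and do not call a single-site configuration sufficient. This accompanies the first step and does not replace it.
3. **Wording.** Replace the claim of a guarantee with wording such as: consistently observed with high performance in these sites. Drop the phrase about no chance of success. Present solutions that shuffled data often match as hypothesis-generating only.

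The six to eight conditions can stay. The cost is analyst time, including writing the screening criteria as a rule that can be repeated by program; no new data are needed. The downside is that some apparent solutions will be reported as compatible with chance. Reported descriptively, the check fits an aim without hypothesis tests.
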